## Abstract

Forced displacement heightens mental health risks for children, including psychological, environmental and economic stressors, yet few interventions address whole-family needs within humanitarian contexts. Family-systemic approaches show promise, but evidence on interventions addressing social determinants of mental health remains limited. We will conduct a single-masked, two-arm randomised controlled trial with 550 families in East Amman, Jordan, to evaluate StrongerTogether, a modular whole-family intervention with a financial literacy component. Families experiencing multiple psychosocial challenges will be randomised 1:1 to receive the intervention or enhanced treatment as usual. The trial employs sequential dual outcomes testing, evaluating effectiveness through: (1) upstream improvements in at least one of three primary outcomes (family functioning, parenting practices and caregiver mental health) and (2) direct improvements in adolescent mental health among those with elevated baseline distress. We will also evaluate two implementation tools: ReachNow for family case detection and FamilyACT for facilitator competency assessment. A mixed-methods process evaluation will examine implementation, effectiveness and potential sustainability of core and optional modules. This will be the first rigorous evaluation of an integrated whole-family intervention addressing social and environmental determinants of mental health in humanitarian settings. Findings will inform evidence-based approaches to family mental health support and contribute validated tools for implementation at scale.

## Impact statement

Over 122 million people worldwide are forcibly displaced, with children and families facing devastating mental health consequences that persist long after initial displacement. This research addresses a critical gap by rigorously evaluating a whole-family mental health intervention designed specifically for humanitarian contexts that addresses commonly experienced stressors, including conflict, parenting difficulties, mental health concerns and economic stressors: all major drivers of family distress. Unlike many focused mental health approaches that treat psychological symptoms in isolation, StrongerTogether recognises that refugee families face interconnected challenges requiring integrated solutions. The integration of financial literacy components represents an innovative approach to addressing the root causes of family distress. This holistic model could transform humanitarian approaches to family well-being towards comprehensive support that addresses families’ complex realities. The research will also produce validated tools for identifying families in need and assessing facilitator competencies, practical resources that can be immediately adopted by implementing organisations. For policymakers and practitioners, this research offers evidence-based, accessible mental health support and implementation tools that can be delivered by trained community members, making it sustainable and scalable.

## Introduction

### Background and rationale

By the end of April 2025, 122.1 million people were forcibly displaced worldwide (UNHCR, 2025). Refugees and asylum seekers experience significantly higher rates of mental illness, with lasting impacts on children’s mental health, cognitive development and behaviour (Chen et al., 2019; Blackmore et al., 2020a, 2020b; Arakelyan and Ager, 2021). This situation underscores the critical need for mental health and psychosocial support (MHPSS) interventions for displaced and conflict-affected populations.

Displacement not only impacts children individually (*e.g.*, through experience of traumatic events), it also exposes them to adverse social circumstances, which negatively affect mental health (Scharpf et al., 2021). For example, the fracturing of social and economic structures, combined with harsh living conditions and diminished coping resources, exposes children to increased violence and neglect within their homes and communities (Rubenstein et al., 2020). These environmental stressors undermine family functioning, exacerbating parental distress, family conflict and harsh disciplinary practices (Wessells et al., 2017; Eltanamly et al., 2021). Caregivers struggling with their own mental health challenges may adopt harmful parenting behaviours, creating a cyclical pattern that further compromises child well-being (Saile et al., 2014; Bryant et al., 2018; Rajan et al., 2022).

However, the caregiver–child relationship can also serve as a major protective mechanism, with supportive family environments mitigating against displacement-related adversities. In line with family systems theory, higher family functioning and nurturing relationships have been found to be strong protective factors for both child and caregiver mental health and well-being (Scully et al., 2020). A recent systematic review examining mental health outcomes among forcibly displaced children and families highlights that family cohesion, nurturing parent–child relationships and consistent parental support monitoring can contribute to youth resilience and well-being (Scharpf et al., 2021). This protective effect can also extend to caregivers, with a bidirectional relationship found between caregiver mental health, parenting and child mental health (Pardini, 2008; Sim et al., 2019).

### Whole-family interventions

#### Caregiver- and family-focused interventions

The protective potential of healthy family systems for child outcomes has driven an interest in family-focused interventions in low- and middle-income countries (LMICs) and humanitarian settings (Tol et al., 2011; Giusto et al., 2025). Substantial evidence demonstrates that caregiver-focused interventions can improve parent–child relationships and enhance both caregiver and child mental health across diverse contexts (Vlahovicova et al., 2017; Pedersen et al., 2019; Backhaus et al., 2023; Bosqui et al., 2024). These interventions often work with only caregivers, emphasising caregiver psychoeducation and coping skills development, as well as family-based homework activities.

Significant gaps remain in comprehensive whole-family interventions for mental health in humanitarian contexts. While existing parenting interventions in humanitarian settings effectively reduce violence and improve mental health outcomes (Backhaus et al., 2024), they predominantly address single issues rather than adopting holistic approaches addressing multiple family stressors. The few existing family-focused interventions designed for humanitarian settings rarely address mental health within the broader context of its social determinants, such as economic hardship (Bunn et al., 2022). While direct provision of economic support typically falls outside the scope of focused MHPSS interventions, ‘structure-sensitive’ approaches, or support that acknowledges and works within the broader constellation of family stressors (Patel, 2025), can provide meaningful support through acknowledging families’ real-world concerns and strengthening their coping strategies. This goes beyond most clinical interventions, which only focus on intra-psychic processes (Miller et al., 2021).

#### Addressing social and environmental determinants of mental health

Recent priorities in both research and practice emphasise the need for integrated, multi-sectoral approaches to MHPSS that deliver multilayered systems of care to affected populations to address psychological, social and environmental determinants of health (Lund et al., 2018; Bosqui, 2020; Tol et al., 2023; Giusto et al., 2025). Despite this recognition, the majority of existing MHPSS interventions in LMICs focus on prevention and response at the individual and interpersonal level (*e.g.*, integrating cognitive behavioural therapy and parenting education), failing to address environment-level drivers of poor mental health (Pedersen et al., 2019; Bosqui et al., 2024). Evidence on effective, integrated interventions in humanitarian settings remains particularly limited. While several evidence-based interventions targeting interpersonal violence against children and gender-based violence have integrated MHPSS components into caregiver- and family-focused interventions for conflict-affected families (*e.g.*, Puffer et al., 2017; El-Khani et al., 2021; Sim et al., 2021; Hillis et al., 2024), very few economic programmes have integrated MHPSS components (*e.g.*, Glass et al., 2020; Moyano et al., 2024). Notably, no focused humanitarian MHPSS programmes to date have integrated economic or financial programming. This gap persists despite increasing uptake of the Minimum Services Package for MHPSS (Inter-Agency Standing Committee [IASC], 2022), which demonstrates the demand for the integration of MHPSS across humanitarian sectors. This presents an opportunity for MHPSS interventions to adopt structure-sensitive approaches that, while not providing direct economic assistance, can acknowledge financial stressors as part of the family’s social and environmental context and offer practical skills for financial management within constrained resources. This is a step toward more systematically addressing stressors or social determinants of mental health.

#### Implementation challenges and the need for standardised tools

Notwithstanding growing evidence for the effectiveness of family-focused MHPSS interventions in humanitarian settings, significant challenges remain in translating research findings into scalable, real-world implementation. Key barriers to increasing the reach and adoption of mental health interventions when scaling beyond controlled trial conditions affect both supply and demand. For example, training and supervising sufficient non-specialist facilitators while maintaining quality standards (Troup et al., 2021), and difficulties identifying and engaging families where mental health literacy, help-seeking behaviours and services may be limited (Kazdin, 2019).

The development of standardised implementation tools represents a critical gap in MHPSS research and practice (Giusto et al., 2025). Individual- and community-level case detection tools have demonstrated accuracy in identifying children and adults needing mental health care (*e.g.*, Jordans et al., 2017; Subba et al., 2017; van den Broek et al., 2021, 2023); however, family-level case detection tools have yet to be validated (Brown et al., 2024). Similarly, while validated competency assessment frameworks have been applied in several caregiver-focused (Martin et al., 2021) and psychological interventions for adults and children (Kohrt et al., 2025; WHO, 2025), structured approaches to assess competencies for working with whole families remain underdeveloped (Brown et al., 2022). The rigorous evaluation of implementation tools alongside intervention effectiveness represents an important contribution to implementation science (Proctor et al., 2023), potentially improving both the quality and scalability of family-focused MHPSS interventions in humanitarian settings.

#### Developing a whole-family approach for refugee families in the Middle East

To address these critical gaps, StrongerTogether, a whole-family intervention intended to improve family-system interactions (‘family-systemic’), was developed to improve family functioning and adult and child mental health. The intervention consists of seven core sessions and four optional modules that aim to match the specific concerns raised by individual families (Bosqui et al., Under review).

Previously, a fully powered randomised controlled trial (RCT) evaluating core sessions of the intervention with 351 refugee families in Lebanon demonstrated significant improvements in family functioning, adolescent well-being, caregiver mental health and positive parenting practices (Brown et al., 2022; Bosqui et al., Under review). Next, a feasibility RCT evaluating the intervention consisting of the core sessions plus three optional modules selected by each family was conducted with Syrian, Iraqi and Jordanian families (*n* = 60 families) to confirm the intervention’s feasibility, acceptability and relevance, as well as feasibility of study procedures (Brown et al., 2024). Following this feasibility trial, recognising the profound impact of economic stressors on families’ well-being, the final iteration of StrongerTogether included an optional financial literacy component, which was developed and tested through a pilot case study (*n* = 20 families) as part of the feasibility trial. This progressive development reflects a commitment to addressing the complex, interrelated challenges faced by families in humanitarian contexts through a holistic, modular approach impacting immediate psychological needs while being sensitive to underlying social determinants of mental health. Evidence of the effectiveness of the core intervention and its optional components through a fully powered RCT is now needed.

### Objectives and hypotheses

The primary aim of this study is to evaluate the impact of a whole-family intervention on social and contextual determinants of adolescent mental health (family functioning, parenting behaviours and caregiver distress) and subsequently adolescent mental health problems among forcibly displaced and socio-economically vulnerable families living in Jordan. Given that the intervention is intended to impact the entire family system, we will use a sequential testing approach to evaluate the effect on outcomes at multiple levels (*i.e.*, for different family members). Secondarily, it will evaluate the adapted versions of two tools for implementation of whole-family interventions for mental health: FamilyACT for assessing facilitator competency, and ReachNow for proactively selecting families in need of focused, non-specialist mental health support. The process evaluation aims to illuminate the effectiveness of the core and optional modules and mechanisms of change in addition to assessing their implementation and potential sustainability.

#### Primary effectiveness hypotheses

StrongerTogether will demonstrate effectiveness through sequential testing of dual pathways:H1 (upstream mechanisms): Families receiving StrongerTogether will show significantly greater improvements in at least one upstream determinant (family functioning, parenting practices or caregiver mental health) compared to enhanced treatment as usual (ETAU) families at endline (T2).H2 (direct effects in high-need families): Among families with adolescents showing elevated baseline distress (emotional and/or behavioural difficulties), the intervention will demonstrate superior effectiveness in reducing adolescent distress compared to ETAU at endline (T2).H3 (moderation effect on downstream outcome): The intervention will strengthen the protective relationship between upstream improvements and adolescent mental health, such that treatment families demonstrate greater child mental health benefits from upstream improvements in family functioning, parenting practices or caregiver mental health compared to control families at endline (T2) and follow-up (T3).

The study is fully powered to test H1 (power = 0.85). H2 and H3 are positioned as exploratory analyses, given limitations regarding sample size (see below for sample size calculation).

#### Primary implementation hypotheses

The ReachNow tool will accurately identify 70% or more of families in need of focused mental health support as identified through screening results. In addition, the FamilyACT tool will demonstrate adequate reliability and validity for assessing facilitator competencies in delivering family-systemic interventions in humanitarian settings.

The study will secondarily explore mechanisms of change of the intervention through mixed-methods exploratory longitudinal analyses.

### Trial registration

The study will be prospectively registered with ISRCTN in accordance with the Standard Protocol Items: Recommendations for Interventional Trials 2025 checklist (Chan et al., 2025).

## Methods

### Study setting

The study will take place in East Amman, Jordan. Jordan hosts the second largest population of refugees *per capita* globally, with an estimated 1.3 million refugees and asylum seekers (UNHCR, 2024a) in a total population of ~11 million (United Nations Jordan, 2022). Over 80% of the refugees in Jordan have settled in urban and peri-urban areas outside of formal camp settings (UNHCR, 2024b). East Amman is one of the most densely populated areas in Jordan, with the neighbourhood of Hashmi Shamali home to over 200,000 refugees from six different countries as of May 2025.

Many refugees in Jordan experience severe psychological distress, with two-thirds meeting symptom criteria for depression, anxiety or posttraumatic stress disorder (Nazzal et al., 2024). Displacement-related distress is exacerbated by overlapping stressors, including insecure income and housing, inaccessible services, disrupted social support, exploitation and discrimination (Wells et al., 2016; Chen et al., 2019; Barrett et al., Under review). The burgeoning humanitarian population has overwhelmed public systems within Jordan, where long-term regional instability and economic hardship have diminished the country’s health, education and economic systems. This has resulted in a high level of unmet need for MHPSS for populations facing chronic adversity. Jordan’s Ministry of Health emphasised the need for family-based psychosocial support within East Amman, specifically (World Health Organization, 2024).

This study is a partnership between War Child Alliance, SOS Children’s Villages Jordan, University of Copenhagen, and the University of Jordan. Both StrongerTogether and ETAU will be implemented by two community-based organisations: the Families Development Association in Al Hashmi Al Shamali and the Nawafez Al Ata’ Association (Windows of Giving) in Tabarbour, near the Al Hashmi Al Shamali area.

### Trial design

The study is a single masked, two-arm RCT with an embedded qualitative process evaluation. Families will be randomised to the intervention or ETAU arms in a 1:1 allocation ratio. Outcomes will be assessed at baseline prior to randomisation (T0), at midline after the completion of core sessions (T1), at endline after the completion of advanced modules (T2, primary time point) and at follow-up 6 months after endline (T3).

The trial employs a sequential, dual outcomes approach to establish effectiveness through multiple pathways comparing treatment *versus* control conditions: (1) upstream improvements in family functioning, parenting practices or caregiver mental health in the full sample; (2) direct improvements in mental health in high-distress adolescents; or (3) enhanced protective effects of upstream improvements on adolescent mental health. Secondary exploratory analyses will examine mechanisms of change over time and the additive effect of the optional modules compared to core modules.

The embedded process evaluation will evaluate implementation, effectiveness and potential sustainability of core and optional modules through mixed methods, including surveys, programme monitoring, staff debrief meetings and qualitative interviews and focus groups. Qualitative activities will be conducted post-intervention (T2) with families who complete and drop out of the intervention, facilitators, outreach staff and other key personnel.

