#### Randomisation

Randomisation will occur after baseline assessments. Families will be randomly allocated to treatment or ETAU conditions in a 1:1 ratio. A computer-generated randomisation sequence will be created by an independent statistician external to the study location using Research Randomizer (randomizer.org). Complete, temporal participant lists will be provided to the independent statistician, who will match them to the randomisation sequence and return allocations for implementation.

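### H3 is listed as a route to establish effectiveness, but it contrasts slopes on a post-randomisation variable, does not measure adolescent benefit, and is called exploratory elsewhere

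*Protocol article*

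**What the plan says.** Two places give H3 a role in showing effectiveness.

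- Protocol article, Trial design: "The trial employs a sequential, dual outcomes approach to establish effectiveness through multiple pathways". Three pathways follow, joined by a disjunction, and the third is "or (3) enhanced protective effects of upstream improvements on adolescent mental health".  Exploratory analyses come in a separate sentence after this list.
- Protocol article, Primary effectiveness hypotheses: the lead-in is "StrongerTogether will demonstrate effectiveness through sequential testing of dual pathways". H1, H2 and H3 follow. H3 reads "The intervention will strengthen the protective relationship between upstream improvements and adolescent mental health". The article then spells this out as adolescents under StrongerTogether gaining more from a given upstream change than those under ETAU, both at T2 and at T3.

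Four places point the other way.

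- The paragraph after H3 says that the study is powered for H1 and that H2 and H3 are exploratory because of sample size.
- Statistical analysis puts moderation among the secondary exploratory analyses.
- The Discussion repeats the exploratory status.
- The abstract describes two elements only: upstream improvement, and direct improvement in adolescents with elevated baseline distress.

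On timing, the Randomisation section states: "Randomisation will occur after baseline assessments". On testing, Statistical analysis uses p < 0.05 at each step and goes on to the next step whatever the last one showed.

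**The concern.** H3 asks whether adolescent mental health tracks upstream improvement more steeply under StrongerTogether than under ETAU. Improvement from T0 is a post-randomisation variable, and the three upstream measures are the H1 outcomes that the intervention is meant to change. Families who improve under one arm need not be comparable with families who improve under the other, so randomisation does not protect the contrast.

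The contrast also answers a different question from whether adolescents did better. A difference in slopes says nothing about the difference in means. Under the Trial design wording, H3 alone could support a statement that effectiveness was established even if mean SDQ was equal or worse in the intervention arm. Nothing in the article makes H3 conditional on a mean adolescent benefit.

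**Working it through.** **Plan's own figure.** There is none for H3. The only planning input used here is the analysed size of 220 per arm from Sample size. Whether that size is adequate for H1 is a separate matter.

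**Set-up (all assumed).** M is upstream improvement (higher is better) and Y is adolescent SDQ in SD units (higher is worse). The model is Y on arm, M and arm × M, with robust standard errors and a two-sided 5% test. There are 4,000 simulated trials per scenario. H3 counts as met favourably when the treated slope is significantly more negative; the nominal rate is 2.5%. The article does not give H3's model or the interval defining improvement, so this is one natural reading.

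**Closed form for one mechanism.** Let an unmeasured family trait correlate λ with M and −g with Y, with no causal effect of M on Y. The slope in an arm is −gλ, and its variance is about (1 − g²λ²)/220.

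- λ = 0.2 control and 0.7 treated, g = 0.5: slope difference = −0.5 × (0.7 − 0.2) = −0.25. SE = √[(0.99 + 0.8775)/220] = 0.092. z = 2.71, so the favourable rate is Φ(2.71 − 1.96) ≈ 0.77. Simulated: 78.4%.
- λ = 0.2 and 0.5, g = 0.3: slope difference = −0.09, SE = √[(0.9964 + 0.9775)/220] = 0.095, z = 0.95, rate Φ(−1.01) ≈ 0.16. Simulated: 16.7%.

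**Simulated results.** The last column is the share of trials in which the direct randomised comparison of mean Y significantly favours treatment.

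| Scenario | H3 met favourably | Direct comparison favourable |
|---|---|---|
| No confounding | 2.5% | 2.6% |
| Common cause, equal in both arms (λ = 0.4, g = 0.5) | 2.8% (5.2% two-sided) | 2.5% |
| Trait linked 0.2 vs 0.5; g = 0.3 / 0.5 | 16.7% / 38.2% | 2.9% / 2.5% |
| Trait linked 0.3 vs 0.6; g = 0.3 / 0.5 | 16.3% / 37.7% | 2.6% / 2.3% |
| Trait linked 0.2 vs 0.7; g = 0.3 / 0.5 | 36.6% / 78.4% | 2.5% / 2.4% |
| 0.2 vs 0.7, g = 0.5, treated arm 0.2 SD worse | 77.5% | 0.0% |
| Shared reporting component in treated arm only, 0.3 / 0.5 / 0.7 SD | 14.4% / 57.8% / 93.4% | 2.4% / 2.1% / 2.2% |
| Reliability of M 0.5 control vs 0.9 treated, same true slope −0.4 | 57.8% | 2.2% |
| Real slope difference of −0.3, mean effect zero | 88.4% | 2.5% |
| True benefit 0.25 SD wholly through M, equal slopes | 2.2% | 74.5% |

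The last row checks by hand. M shifts by 0.5 and the slope is −0.5 in both arms, so the benefit is 0.25. With SE = √(2/220) = 0.095, z = 2.62 and Φ(2.62 − 1.96) ≈ 0.75. The slope difference is zero, so H3 stays at its nominal rate.

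**Number of tests.** Three upstream variables at two time points allow up to six tests. If all six were run and independent, the chance of at least one false positive is 1 − 0.95⁶ = 26.5%, or 1 − 0.975⁶ = 14.1% in the favourable direction, which is what H3 claims. The article does not say how many tests will be run.

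**Could the arms differ in this way?** Masking concedes that participants cannot be fully masked. The primary SCORE-15 and the primary SDQ are both adolescent-reported, so reporting error could be shared and could differ by arm. This applies to one of the three upstream measures only; parenting practices and the K10 are caregiver-reported.

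**The case against.** The strongest defence is that the article already disarms H3. It is called exploratory directly beneath its definition, moderation is secondary in Statistical analysis, the Discussion points to future mechanistic studies, and the abstract leaves the third route out. Adolescent SDQ is the primary downstream outcome, so an adverse mean would be reported beside H3. The H3 model may be set out in an analysis plan not shown here.

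Much of this stands, and it rules out several stronger readings.

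- A reader might infer that the sponsor will declare success on H3 alone. The exploratory statements do not support that; the wording permits such a claim but does not announce it.
- A reader might infer that a post-randomisation moderator inflates the error rate by itself. It does not: with a common cause equal in both arms the test stays at 5.2%. Inflation needs confounding, reporting or measurement error that differs by arm, and its size cannot be had from the article.
- A reader might assume that upstream change and SDQ come from the same visit. The article gives T2 and T3 for H3 but not the interval defining improvement.
- The lack of a named mediation model is not a defect, since that belongs in the analysis plan.

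The defence does not remove the conflict. The exploratory label is justified by sample size, and more families would not turn the slope contrast into a randomised comparison. Reporting an adverse mean is not the same as requiring a favourable one.

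**Conclusion.** The point holds as a conflict in the stated role of H3, with a real inferential consequence. Trial design and the primary hypotheses let H3 establish effectiveness; the exploratory statements and the two-pathway abstract do not. Both Trial design and the hypotheses section speak of a dual approach and then list three items.

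The slope contrast should not carry an effectiveness claim in either direction. It can be significant with no mean benefit, or with harm, when confounding, shared reporting or measurement error differs by arm. Even a genuine slope difference can go with a mean effect of zero. It can also miss a benefit that works through upstream change with equal slopes, which is the mechanism the trial is built around. The percentages above show what is possible under assumed inputs; they do not estimate this trial's error rate. H1, the powered hypothesis, is unaffected.

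**What to change.** 1. In Trial design, delete pathway (3) from the routes to establishing effectiveness.
2. Move H3 out of Primary effectiveness hypotheses and place it with the secondary exploratory analyses.
3. State that H3 is an exploratory, non-causal mechanism analysis because its moderator is a post-randomisation outcome, and not only because of sample size.
4. State that any claim of adolescent benefit rests on the randomised between-arm comparison of adolescent-reported SDQ.

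The choice of mediation or moderation model can be left to the statistical analysis plan. One caution for that choice: change measured at T1 alone would miss the optional modules, which are delivered after T1 and cover parenting and caregiver mental health.

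The cost is a wording change and the loss of one nominal route to an effectiveness claim. No new data, visits or participants are needed.
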